### Participant timeline

The OPTIM study is part of the routine care of patients at geriatric/memory center. Four successive evaluations are planned for the participants (Table 1). The inclusion is planned at the first consultation of the patients at the geriatric/memory center. Three others evaluations during follow-up are planned: at 1 month and after 6 months and 18 months. At 6 and 18 months, the patients will undergo a consultation at the geriatric/memory center, whereas the limited evaluation at 1 month will be performed by phone with the primary caregiver.

**Table 1 Tab1:** Schedule of enrolment, intervention and assessments of the OPTIM study

	Study Period				
	Enrolment	Allocation	Follow-up		
Timepoint	- *t1*	0	*t* _*1*_ *: 1 month*	*t* _*2*_: *6 months*	*t* _*3*_: *18 months - Close-out*
Enrolment:					
Eligibility screen	X				
Information to patients/careviger	X				
Collection of non-opposition to participate	X				
Randomized allocation		X			
Intervention:					
*(1) Intervention: Optimization of drug prescribing*		X	X	X	
*(2) Control*					
Assessments:					
*Collected in patient record:* * Sociodemographic data * Diagnosis and stage * Current comorbidities, history of comorbidities, lifestyle habits * Biological exam and artrial pressure when available		X			
*Primary outcomes:* * IADL scale * DAD-6 scale		X	X	X	X
*Secondary outcomes:* * MMSE (cognitive function) * mini-GDS (depression) * Hamilton scale (anxiety) * Pain scale * EUROQOL-5D (quality of life) * Girerd scale (compliance to drug prescribing) * Event and date of event: hospitalization, falls, recourse of emergency, institutionalization, death		X		X	X
Drugs prescribing		X	X	X	X

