### Outcomes

The primary outcome will be the evolution of patients’ functional autonomy level assessed with two scales: The Instrumental Activities of Daily Living (IADL) scale of Lawton and the 6-item Disability Assessment of Dementia (DAD-6) scale. Each scale will be analyzed separately. The evolution of functional autonomy will be calculated using the successive evaluations of the scales. The IADL scale assesses the level of functional autonomy of a patient through the assessment of instrumental activities of daily living including ability to use the telephone, transportation, shopping, managing medications, manage a budget, prepare meals, maintain the house and do the laundry. The rating scale provides a score from 0 to 8. A higher score indicates a higher level of dependency, while a lower score reflects a lower level of dependence. The IADL scale consists of 8 questions. The DAD-6 assesses the patient’s activities in his daily life. It includes six questions assessing the degree of autonomy for the following activities: Food, use the telephone or the computer, moving outside, finance and correspondence, medications, leisure and home maintenance. The score ranges from 0 to 18 points, the higher the score is, the more the patient is autonomous. The IADL and DAD-6 scales will be collected during an interview between the patient’s primary caregiver and a neuropsychologist, a nurse or a physician.

The secondary outcomes collected for patients will be the occurrence and the number of all-cause hospitalizations and all-cause emergency department visit after inclusion, admission in institution, and the delay before institutionalization, the occurrence and number of falls after inclusion, the overall cognitive function estimated by the Mini Mental Sate Examination (MMSE) [38] at baseline and its evolution assessed using the successive measures performed at each visit, the quality of life of the patients measured by the questionnaire EUROQOL 5D (EQ5D) [39], the depression and anxiety disorders measured respectively with the mini-GDS scale [40], and the Hamilton scale [41], the compliance of patients with treatment measured with the Girerd questionnaire [42], pain measured with an ordinal scale from 0 to 10, and the possible occurrence of all-cause death. The secondary outcomes collected for RP will be the number of PIP after intervention, and the type of DRP.

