### Data collection, management, and statistical analysis

#### Data collection methods and data management

The clinical data are collected in a case report form (CRF) assigned to each patient, referred by a unique numeric identifier, using the patient medical record and during the consultation, by a trained neuropsychologist or nurse. Primary and secondary outcomes are collected during the assessment at the consultation. Data are then entered into a computerized database by the neuropsychologist or the nurse. Drugs are collected by the clinical pharmacist using the RP prescriptions and those of the specialist physician at hospital after the consultation. Drugs data and pharmaceutical analysis and PI are entered in the computerized database by the clinical pharmacist. The data collected in the CRF and in the database will be verified for accuracy, missing data, and data consistency with the documents ‘source’ (medical records, visits schedules). Data quality will be analyzed during the study. The completeness and the information will be checked for plausibility in each case report form by a clinical research associate (CRA).

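### Falls and other events are not scheduled at the 1-month caregiver call, so first-month events are first sought at 6 months and those of months 6 to 18 at a single visit

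*Protocol article*

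**What the plan says.** The Protocol article sets the contacts in its Participant timeline section: "Three others evaluations during follow-up are planned: at 1 month and after 6 months and 18 months". The later two are face to face: "At 6 and 18 months, the patients will undergo a consultation at the geriatric/memory center". The first is not: "whereas the limited evaluation at 1 month will be performed by phone with the primary caregiver".

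In Table 1, the primary scales and drug prescribing are marked at inclusion and at 1, 6 and 18 months. The secondary outcomes share one row, marked at inclusion, 6 and 18 months and blank at 1 month. That row ends with "Event and date of event: hospitalization, falls, recourse of emergency, institutionalization, death". The Data collection section agrees with the table: "Primary and secondary outcomes are collected during the assessment at the consultation".

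The Outcomes section turns these events into counts and times. It lists "the occurrence and the number of all-cause hospitalizations and all-cause emergency department visit after inclusion", then "the occurrence and number of falls after inclusion", and also the delay to institutionalization. The analysis section allows Cox models for secondary outcomes. On sources, the Data collection section says that clinical data are gathered "using the patient medical record and during the consultation, by a trained neuropsychologist or nurse".

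**The concern.** The 1-month call already reaches the person best placed to report a fall or an admission. Every patient must be accompanied by a caregiver to be eligible, and that caregiver is interviewed at 1 month for the two primary scales. Some items in the blank row, such as the MMSE, need the patient in front of the assessor. The five event items do not, and the article gives no reason for leaving them out.

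Falls matter most here. The Background names them among the adverse drug events through which better prescribing is expected to protect autonomy, and their number is a listed outcome. A fall with no medical contact need not appear in any record, so its count and date depend on what patient and caregiver remember. In patients attending geriatric and memory consultations, a look-back of 6 or 12 months invites undercounting and misdating. A patient who leaves between the 1-month call and the 6-month visit may contribute no event information, although the caregiver was spoken to in between.

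**Working it through.** The plan states no figure for this point, so there is none to reproduce. The check uses the visit times, N and attrition given in the article.

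**Inputs.** Contacts at 0, 1, 6 and 18 months (Participant timeline); event item marked at 0, 6 and 18 months only (Table 1); 302 patients and 25% expected attrition (Sample size).

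**Look-back windows as planned.**
- Visit at 6 months covers months 0 to 6: 6/18 = 33% of follow-up.
- Visit at 18 months covers months 6 to 18: (18 − 6)/18 = 12/18 = 67% of follow-up.
- An event in the first month is first asked about between 6 − 1 = 5 and 6 − 0 = 6 months after it happens.

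**Look-back windows if the 1-month call also asks about events.**
- Months 0 to 1: at most 1 month.
- Months 1 to 6: at most 5 months.
- Months 6 to 18: still up to 12 months, because no contact is added there.

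**Patients who leave before month 6.** Expected attrition is 302 × 0.25 = 75.5 patients. The article does not say when they leave, so the share s leaving before the 6-month visit is an assumption, and the number affected is 75.5 × s:
- s = 0: 0 patients
- s = 0.25: 18.9, about 19 (6% of 302)
- s = 0.50: 37.75, about 38 (13% of 302)
- s = 1: 75.5, about 75 (25% of 302)

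These are patients without event collection at a post-baseline visit. They are not necessarily patients without event data, since a record may hold some of their events. With the change, each of them reached at 1 month would add one month of event follow-up. Under Harms – End of protocol, data gathered before withdrawal may be used, so that month would count.

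**Which events are exposed.**
- Death does not depend on recall.
- Hospitalizations and emergency visits can be checked at least partly in records.
- Falls without medical contact are the main item with no second source.

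Separately, Table 1 marks the intervention at 0, 1 and 6 months, while the Interventions section places the medication review at inclusion, 6 and 18 months. Those passages must be reconciled, but this point does not depend on which one stands.

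**The case against.** The strongest reply is that little is lost. The outcomes count events since inclusion and Table 1 asks for their dates, so a first-month event is due at the 6-month visit. The medical record is a source alongside the consultation, and entries are verified against source documents. Patients who miss a visit are contacted, and they remain in follow-up unless they withdraw. The blank cell belongs to a row bundling patient-tested scales with events, so it may reflect the limits of a phone call more than a decision to ignore events. These are secondary outcomes in a trial described as exploratory, and the primary scales are collected at 1 month.

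Most of this stands, and it limits the point. It does not answer two things. A record of medical contacts will not supply falls that led to none. And the procedure described for a missed visit is to propose another visit or record the reason for absence; collecting events is not mentioned.

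A reader might go further and infer that early harm from drug changes is lost and that the programme will look safer than it is. The article does not support that, for three reasons:
- For patients who reach month 6, the issue is late ascertainment, not loss.
- The referent physician may or may not apply the recommendations and no date is given for any change, so it cannot be assumed that prescriptions have changed by month 1.
- The programme is expected to reduce these events. Under-recall that is similar in both arms would hide a benefit as readily as a harm. Because the trial is open-label, recall could also differ by arm, and the direction of that error is not known.

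**Conclusion.** The point holds as a modest, inexpensive improvement to the schedule. Table 1 omits the event item from a caregiver call that is already made, so first-month events wait 5 to 6 months to be asked about, and 67% of follow-up rests on one visit. The weakness falls mainly on the number and dates of falls, and on early events in patients who leave before month 6. The size of that second group cannot be fixed from the article: it runs from 0 to about 75 of 302, depending wholly on an attrition timing that is not stated. The amount of under-recall is likewise not given, and the direction of any resulting error is open. The primary outcome is unaffected. The conclusion assumes that Table 1 and the Data collection section describe event collection as it will be done, and that a caregiver can answer the event items by phone.

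**What to change.** In Table 1, separate the event item from the patient-tested scales and mark it at t1. Ask the five event items, with dates, on the existing 1-month call, in the same way in both arms. Amend the sentence in the Data collection section that ties outcome collection to the consultation so that it includes this call.

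This cuts the look-back for first-month events from up to 6 months to at most 1, and keeps that month for patients who later leave. It does nothing for the 12 months between the last two visits. For that period, a one-page dated event sheet given to caregivers at inclusion is an optional low-cost aid.

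The cost is a few minutes of caregiver and data-entry time per patient and one added CRF page, plus one paper sheet per caregiver if the optional aid is used. No treatment or visit changes.

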### Sample size

The number of subjects needed was calculated on the primary outcome (IADL) to demonstrate a significant difference in the evolution of functional activities between the intervention group and the control group. The IADL score in patients aged 70 years deteriorates on average of 16% over a period of 18 months. This evolution would represent a change of 1.3 percentage points (SD 2) expected in the control group in our study population. To highlight a 20% difference of the evolution of this score, equivalent to a change of 1.04 points of IADL in the intervention group, for an alpha = 0.05 and a power of 80% (two-tailed test), it is necessary to include 224 patients (112 per group). A first observation made in the Charpennes Hospital showed that RP referred 2 patients in average at the memory center. Taking the conservative assumption of 4 patients on average per referent physician, the inflation factor applied was 1.03 for an intra-class coefficient (ICC) of 0.01 [43, 44]. Taking into account the ICC, the number of subjects needed was 232 patients spread between the 2 study groups. Finally, the number of subjects required was corrected for an expected attrition rate of 25%; the corresponding correction factor was 1.3. Assuming that the rate is the same in the 2 groups, the number of subjects required was 302 patients.

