**Methods:**

A multicenter, open-label, Randomized Controlled Trial was designed to assess the impact of an optimization program of drug prescribing consisting in a clinical medication review by a pharmacist, in collaboration with specialist physician of the geriatric/memory center and the referent physician, on the evolution of functional autonomy level, measured during 18 months of follow-up. The study will include 302 elderly outpatients visiting geriatric and memory centers, randomly distributed in one of the two parallel groups. One group will benefit of the intervention, while the other will be considered as control group. The effect of the intervention on evolution of the level of autonomy function, defined with repeated measures, will be estimated in a generalized linear mixed model. The intervention will be considered significant if the interaction between time and the study group is significant. Secondary analysis will be conducted to assess the impact of the intervention on secondary clinical outcomes.

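### The stated inputs need 929 patients per group, not 112; with 112 per group the power for the trial's own target difference is about 16%, not 80%

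*Protocol article*

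**What the plan says.** All the inputs stand in one paragraph, the Sample size section of the protocol article.

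- Control group: "This evolution would represent a change of 1.3 percentage points (SD 2) expected in the control group in our study population". The unit must be scale points. The paragraph takes a 16% deterioration, the Outcomes section says "The rating scale provides a score from 0 to 8", and 0.16 × 8 = 1.28.
- Intervention group: "To highlight a 20% difference of the evolution of this score, equivalent to a change of 1.04 points of IADL in the intervention group".
- Error rates: "for an alpha = 0.05 and a power of 80% (two-tailed test)".
- Result: "it is necessary to include 224 patients (112 per group)".

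The section then multiplies by 1.03 for patients sharing a referent physician (ICC 0.01, 4 patients per physician) to reach 232. For 25% attrition it says that "the corresponding correction factor was 1.3", which gives 302. The abstract repeats the total: "The study will include 302 elderly outpatients". No other SD, no correlation between visits and no variance reduction is given.

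The primary analysis, in the section on comparative analyses of the primary outcome, is a mixed model over the repeated assessments. The intervention is judged by the time-by-group interaction. Table 1 places the IADL at baseline and at 1, 6 and 18 months.

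**The concern.** A difference of 0.26 points against an SD of 2 is a standardised effect of 0.13. An effect that small normally needs close to a thousand patients per group, so 112 looks wrong on sight.

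The whole enrolment target of 302 rests on the 224. If the trial ends without a significant interaction, a reader who trusts this paragraph will believe it had an 80% chance of showing a 20% slowing. On the stated inputs it would miss such an effect about 84% of the time, so the null result would say almost nothing about it. Conversely, if the true effect is near 0.26 points, an estimate can reach significance only by being about twice as large as the truth.

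**Working it through.** **Inputs (Sample size section).** Control change 1.3; intervention change 1.04 (0.80 × 1.3); SD of the change 2; two-sided alpha 0.05 (z = 1.960); power 80% (z = 0.842); equal groups.

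**1. The plan's later steps.** 112 × 1.03 = 115.4, so 116 per group and 232 in total, as stated. 232 × 1.3 = 301.6, so 302, as stated. The inflation from 224 onward can be followed; the starting figure cannot.

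**2. Patients needed for the stated difference.**
Difference = 1.3 − 1.04 = 0.26.
n per group = 2 × (1.960 + 0.842)² × (2/0.26)² = 928.9, so 929 per group and 1,858 in total. The t-based calculation gives 930 per group. The stated 112 is smaller by a factor of 929/112 = 8.3.

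**3. Power at the stated size.**
Standard error = 2 × √(2/112) = 0.267.
Power = Φ(0.26/0.267 − 1.960) ≈ 0.16 (the lower tail adds under 0.002; the t-based value is also 0.16).

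| Patients analysed | Power for 0.26 points |
|---|---|
| 224 (112 per group) | 16% |
| 302 less 25% = 226.5 | 16% |
| 226.5/1.03 ≈ 220 effective | 16% |
| all 302, no loss | 20% |

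**4. What 112 per group can detect.**
Detectable difference at 80% power = 2.802 × 2 × √(2/112) = 0.75 points, and 0.75/1.3 = 58% less decline.
Smallest significant estimate = 1.960 × 0.267 = 0.52 points, twice the target. The 95% interval half-width is about 0.52 to 0.53 points.
For 112 per group to be right at 0.26 points, the SD would have to be 0.26/(2.802 × √(2/112)) = 0.69.

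**5. Other readings of the inputs (n per group).** One-sided test 732; SD² = 2 gives 465; one-sample formula 465; Poisson means 1.3 and 1.04 give 272; proportions 16% and 12.8% give 1,889; difference taken as 1.04 gives 59; difference taken as 1.3 gives 38. None gives 112.

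**6. Could the repeated measures explain it?** The text attaches SD 2 to the change, so the correlation between baseline and 18 months is already absorbed. Keeping that reading, a linear slope over 0, 1, 6 and 18 months with compound symmetry gives about 19% power. If SD 2 is instead taken as the SD of a single score, power at 112 per group depends on the between-visit correlation:

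| Correlation | Change score | ANCOVA | Four-visit slope |
|---|---|---|---|
| 0.5 | 16% | 20% | 19% |
| 0.7 | 24% | 28% | 29% |
| 0.8 | 34% | 37% | 41% |
| 0.9 | 59% | 61% | 69% |
| needed for 80% | 0.940 | 0.938 | 0.924 |

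**7. Attrition.** A 25% loss needs a factor of 1/0.75 = 1.333, and 232/0.75 = 309.3, so 310. With 302 enrolled, 302 × 0.75 = 226.5 remain, below the 232 the section asks for.

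**8. Enrolment implied by the stated inputs.** 1,858 × 1.03 = 1,914, and 1,914/0.75 = 2,552.

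**The case against.** The strongest reply is that 16% describes a two-group comparison of one change score, whereas the planned analysis is a mixed model on four assessments. The article condenses a fuller protocol, which may hold a correlation or slope variance that leads to 112. This stands in part: the 16% is the power on the printed inputs, and the realised power could be higher. It does not rescue the printed figure. With the SD of change kept at 2, the slope model reaches only about 19%. Under the other reading of SD 2, 80% needs a correlation above 0.92. The paragraph presents its inputs as sufficient for 224, and they are not.

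The trial is also labelled exploratory in the OPTIM trial design section, and the analysis section already promises coefficients with 95% confidence intervals. That softens the consequence. Yet the Sample size section still claims 80% power to show a significant difference, and a significant interaction is still the criterion of success.

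It is fair to say that a significant result need not be an exaggeration: if the true difference were about 0.75 points, the trial would usually find it. The exaggeration arises only if the truth is near the 20% slowing the plan assumes.

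The attrition point is small. The factor 1.3 is 1.333 rounded, a matter of eight patients. A mixed model uses earlier visits from patients who drop out, and 4 patients per physician is a cautious assumption against the 2 observed.

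**Conclusion.** The point holds. The stated difference, SD, alpha and power cannot be reconciled with 112 per group. They require 929 per group, about 8.3 times as many. On the stated inputs the power is about 16% for the 20% slowing, and the design has 80% power only for a difference near 0.75 points (58%). This rests on SD 2 being the SD of the 18-month change, as the sentence reads, and on a two-sided comparison of mean change. The alternatives examined raise the power somewhat, but none supports 80% without an assumption that the article does not state. The attrition factor is a correct but minor side point.

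**What to change.** Rewrite the Sample size paragraph; enrolment can stay at 302.

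1. If 112 came from a different SD or from an assumed between-visit correlation, state that value with its source and recompute from it.
2. If no such input exists, say what 302 delivers: with 25% loss about 226 evaluable patients, roughly 220 effective after the 1.03 design effect, giving about 80% power (79% after the design effect) for a difference of 0.75 IADL points at SD 2, or 58% less decline. Add that the power for a 0.26-point (20%) difference is about 16%.
3. Correct the attrition factor to 1.333 and state that 302 enrolled leaves about 226 patients, slightly under 232. Replace percentage points with IADL points.
4. Add one sentence that a non-significant interaction will be interpreted from the confidence interval and not as evidence that a 20% slowing is absent.

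The cost is rewording and a much less favourable power statement. No patients, visits or analyses are added. Powering the trial for 0.26 points on the stated inputs would instead mean about 2,552 enrolled.

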### Recruitment

Prior estimations of the number of patients visiting the recruiting centers show the capacity of inclusion of the number of subjects needed over 12 months. Several strategies are envisaged to follow up the study population and allow the collection of data. In case the patient does not show up to the consultation of follow-up, the patient will be contacted to propose a new visit or to collect the reason of absence to the consultation.

